## 1. INTRODUCCION and RATIONALE

Obesity and diabetes mellitus type 2 (DM2) are health problems with a tremendous impact. Many attempts have been made to combat obesity and DM2, however, a breakthrough therapy is still lacking.

Obesity is the result of an imbalance between energy intake and energy expenditure. F-fluorodeoxy-d-glucose (F-FDG) positron emission tomography computed tomography (PET-CT) pinpoint areas with high glucose turnover. Physiological F-FDG accumulation is frequently observed in the colon, however, the possibility of the colon as an energy dissipating tissue has not yet been explored. Considering the high uptake of F-FDG in the colon, the colon could have a positive effect on energy balance. Therefore, the colon could become an interesting new target of research to find a method to combat obesity.

Metformin is one of the few drugs in the treatment of DM 2 that is associated with moderate weight loss.

Interestingly, patients using metformin are known to have increased F-FDG-uptake in the colon. A substantial number of subjects (e.g 42%) show an increased F-FDG uptake without the use of metformin. Nonetheless, in a matched case-control analysis, the use of metformin significantly increased physiological accumulation of F-FDG in the colon. Also, discontinuation of metformin in the 2 days before the F-FDG PET-CT, significantly diminished the high F-FDG uptake in the colon. Indeed, the colon has been shown to be a site of increased glucose utilization during metformin treatment in mice. The cause for this increase in glucose uptake in the colon by metformin use is unknown. A possible explanation for increased glucose uptake might be the shift from aerobic to anaerobic glucose metabolism due to the inhibition of the mitochondrial respiratory complex I during metformin use. This mechanism has been proposed as a possible cause of changed intestinal glucose handling and increased production of lactate. This less efficient metabolism might in turn lead to increased heat dissipation. It is unknown whether this increase in glucose uptake in the colon results in an increased energy expenditure and/or an increase in core body temperature.

When core body temperature is measured using a temperature pill, with stable surrounding conditions, core body temperature changes only with very small steps (e.g. a range of 0,2 °C). Furthermore, the ingestible temperature pill has been shown to be a valid manner to measure core temperature. However, in this study we will investigate whether metformin changes the core temperature significantly.

Therefore, we want to measure core temperature, energy expenditure and lactate in lean and obese healthy subjects before and after using metformin.

Furthermore, metformin is known to decrease variables of insulin resistance such as fasting insulin and HOMA-indexes, also among obese adolescents with no associated disease. In

adults with impaired glucose tolerance it has been shown that lifestyle changes can prevent DM2. However, metformin has also been shown to prevent DM2 in adults with impaired glucose tolerance. Therefore, we want to measure insulin sensitivity in obese healthy subjects before and after using metformin using a homa index.

#### *Aim of the study*

The aim of this study is to determine whether metformin modifies the metabolic activity of the colon by an increased glucose uptake and thereby increases temperature. Furthermore, we want to measure energy expenditure, lactate concentration and core body temperature before and after metformin use.

## **2. OBJECTIVES**

**Primary objective:** To investigate whether metformin increases F-FDG uptake in healthy, lean and obese males.

#### **Secondary Objectives:**

- 1) To investigate whether metformin increases core body temperature in healthy, lean and obese males and whether this correlates with respectively F-FDG uptake.
- 2) To investigate whether metformin increases energy expenditure in healthy, obese males and whether this correlates with respectively F-FDG uptake.
- 3) To investigate whether metformin increases core temperature in healthy, obese males and whether this correlates with respectively F-FDG uptake and energy expenditure.
- 4) To investigate whether metformin increases lactate in healthy obese males and whether there is a correlation between lactate and respectively F-FDG uptake, core body temperature and energy expenditure.

### 3. STUDY DESIGN

In this non-randomised intervention study we will study the influence of metformin (1000 mg/day (500 mg in the morning, 500 mg in the evening) during 1 week) on  $^{18}\text{F}$ -FDG uptake in the colon. The main outcome will be difference in  $^{18}\text{F}$ -FDG uptake. Furthermore, we will measure core body temperature, energy expenditure and HOMA-index. 16 healthy volunteers of Caucasian origin will be included (8 lean, BMI < 24 kg/m^2 and 8 obese BMI > 28 kg/m^2) in this study. Subjects (n=16) will be investigated before and after using metformin (1000 mg/day during 1 week). Included subjects will visit the AMC hospital on three occasions. Below is a description of each visit.

#### Study visits and procedures

During the **first** study visit, participants will come to the AMC for screening to determine eligibility for the study. During this visit, informed consent will be obtained after oral and written explanation of the study. Subsequently, length, weight, waist circumference and medical history will be acquired. In total, a maximum of 20 ml of blood will be drawn to perform laboratory measurements needed to determine eligibility for the study (kidney function and liver function). The chronic use of drugs and/or medication will be asked at the participant. If eligible, the second visit will be scheduled.

The **second and third visit** are similar. Core body temperature will be measured using a body core pill and tympanic temperature will be measured every 15 minutes. Blood will be drawn to measure insulin sensitivity, in total 40 ml of blood will be drawn to be able to perform blood tests and as stored serum. After 60 minutes an energy expenditure (EE) will be performed using indirect calorimetry. Glucose uptake in the colon will be evaluated using  $^{18}\text{F}$ -FDG PET CT.

After the **second** visit, subjects will receive the metformin and information on how to use this.

**Flow chart;** overview of the procedures that subjects will undergo in the course of the study.

[figure not shown]

## 4. STUDY POPULATION

### STUDY POPULATION

#### 4.1 Population (base)

16 healthy male volunteers (aged > 50 years, 8 lean (BMI<24 kg/m^2) and 8 obese (BMI> 28 kg/m^2)), will be recruited. Patients will be recruited by public call and advertisement in local papers, covering the wider surroundings of our clinic (Amsterdam).

#### 4.2 Inclusion criteria

- Male
- Caucasian origin
- Subjects should be able and willing to give informed consent
- > 50 years old
- BMI< 24 kg/m^2 or > 28 kg/m^2

#### 4.3 Exclusion criteria

- Renal failure (GFR< 60ml/min)
- Liver insufficiency (AST or ALT 3 times upper value)
- Chronic use of drugs or medication
- Diabetes mellitus
- Lactate acidosis or precoma diabeticum in medical history
- Acute or chronic diseases such as: dehydration, severe infection, shock, heartfailure, pulmonary insufficiency, recent heart attack
- Alcoholism

#### 4.4 Sample size calculation

Based on a retrospective study we have recently performed,[[name], EASD 2014] we aim to find an increase in SUV of 2,8 g/L in the colon. This is an increase from grade 1 to grade 3 based on a visual scale designed by Gontier et al. A sample size of 8 will have 80% power to detect a difference in means of 2,8 (e.g. a First condition mean of 2,7 SUV and a Second condition mean of 5,5 SUV), assuming a standard deviation of differences of 2,24, using a paired t-test with a 0,05 two-sided significance level. To allow for unexpected findings and to increase power we will include 11 subjects per arm.

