**Secondary Objectives:**

- 1) To investigate whether metformin increases core body temperature in healthy, lean and obese males and whether this correlates with respectively  $^{18}\text{F}$ -FDG uptake.
- 2) To investigate whether metformin increases energy expenditure in healthy, obese males and whether this correlates with respectively  $^{18}\text{F}$ -FDG uptake.
- 3) To investigate whether metformin increases core temperature in healthy, obese males and whether this correlates with respectively  $^{18}\text{F}$ -FDG uptake and energy expenditure.
- 4) To investigate whether metformin increases lactate in healthy obese males and whether there is a correlation between lactate and respectively  $^{18}\text{F}$ -FDG uptake, core body temperature and energy expenditure.

**Study design:** Non-randomized interventional study

**Study population:** 16 healthy male volunteers (aged > 50 years, 8 obese BMI > 28 kg/m^2 and 8 lean BMI < 24 kg/m^2) will be recruited. The volunteers will be recruited by advertisement in local paper and internet (via social media), covering the direct surroundings of our clinic (Amsterdam) and by advertisement at the medical faculty of the AMC.

**Intervention (if applicable):** Participants will use metformin during 7 days

**Main study parameters/endpoints:** Difference in F-FDG uptake in the colon before and after using metformin.

**Nature and extent of the burden and risks associated with participation, benefit and group relatedness:** Included subjects will visit the AMC hospital on 3 occasions.

Visit 1: Informed consent, medical history, vital signs, laboratory measurements.

Total blood drawn: 60 ml. Energy expenditure measurement after 60 minutes rest. Core body temperature measurement (core body pill, tympanic measurement and skin measurement).

F-FDG PET CT. Providing the metformin, start using metformin.

Visit 2 (two weeks after visit 1): Energy expenditure after 60 minutes rest. Core body temperature measurement (core body pill, tympanic measurement and skin measurement).

F-FDG PET CT.

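### Section 4.4 plans 11 subjects per arm, while the Summary and Sections 3 and 4.1 plan 16 men (8 lean, 8 obese), so the planned sample size is undefined

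*Protocol*

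**What the plan says.** Section 4.4 sizes the study for the before/after comparison of colonic FDG uptake. It states that "A sample size of 8 will have 80% power to detect a difference in means of 2,8", with the example of "a First condition mean of 2,7 SUV and a Second condition mean of 5,5 SUV", "assuming a standard deviation of differences of 2,24" and "using a paired t-test with a 0,05 two-sided significance level". Its last sentence then sets the enrolment: "To allow for unexpected findings and to increase power we will include 11 subjects per arm".

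Three other places give a different enrolment:

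- Summary, study population: "16 healthy male volunteers (aged > 50 years, 8 obese BMI" and so on, with 8 lean men making up the rest.
- Section 3: "16 healthy volunteers of Caucasian origin will be included (8 lean, BMI" and so on, with 8 obese. The same section repeats n=16 as the number studied before and after metformin.
- Section 4.1: "16 healthy male volunteers (aged > 50 years, 8 lean" and so on, again with 8 obese.

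Three further statements bear on the point. Section 7.4 replaces subjects who withdraw. Section 9.4 plans no interim analysis. The Summary and the Synthesis (11.2) put the radiation dose from the two tracers and scans at 7.8 mSv per participant.

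**The concern.** The planned number of subjects is a basic design figure, and the protocol gives it two values that cannot both hold. No passage reconciles them, and the conflict lies within the current text. A later analysis plan could not settle it, because the number governs enrolment and exposure.

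Three things depend on it:

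- **When recruitment ends.** The study is non-randomised and before/after, and nothing in the design is described as blinded. With two totals in the text, the protocol does not say which one closes enrolment.
- **How many healthy volunteers are exposed.** The men have no direct benefit, take metformin for a week and undergo two PET-CTs.
- **How the result is read.** Whether the study ends at 16 or at 22, a reader could not tell if it kept to its plan.

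**Working it through.** **Step 1. Reproduce the protocol's own figure.** Inputs, all from Section 4.4: difference 2.8 SUV, standard deviation of differences 2.24, two-sided alpha 0.05, paired t-test.

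Standardised effect: d = 2.8 / 2.24 = 1.25.

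Power = P(|T| > t(0.975; n − 1)), where T is noncentral t with n − 1 degrees of freedom and noncentrality 1.25 × √n.

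| n | Noncentrality | Critical t | Power |
|---|---|---|---|
| 7 | 3.307 | 2.447 | 78.6% |
| 8 | 3.536 | 2.365 | 85.6% |
| 11 | 4.146 | 2.228 | 96.1% |

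Eight is the smallest n with at least 80% power, so the stated sample size reproduces.

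**Step 2. Compare the totals.**

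| Source | Per group | Total |
|---|---|---|
| Summary, Sections 3 and 4.1 | 8 lean, 8 obese | 16 (stated) |
| Section 4.4, *arm* = lean or obese group | 11 | 2 × 11 = 22 (inferred) |
| Section 4.4, *arm* = the single treated cohort | not stated | 11 (inferred) |

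The first reading of *arm* is the more natural, because lean versus obese is the only split described. It differs from 16 by 6 men (6/16 = 37.5%). The second differs by 5 men. No reading gives 16.

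**Step 3. Is 11 a recruitment margin around 8 completers?** The text does not support this. Section 3 speaks of 16 subjects being included, the same verb that Section 4.4 uses for 11 per arm. Section 4.4 states no dropout rate, gives unexpected findings and more power as its reasons, and Section 7.4 deals with withdrawals by replacement.

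**Step 4. Exposure.** Under the 22-man reading, 6 further men would take metformin and have two PET-CTs each, at a stated 7.8 mSv per man.

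**Step 5. Worst case for the false-positive rate.** Assumptions: no true effect, normal differences, a paired t-test at two-sided 0.05 at the smaller number, and continuation to a second test at 0.05 at the larger number only if the first is not significant. Simulation with 2,000,000 replicates gives an overall error of 7.6% for 8 then 11 in one group, and 7.6% for 16 then 22 pooled. Separate simulations of the same rule gave 7.5% to 7.7%.

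**The case against.** The strongest reply is that this is one stray sentence. Three places agree on 16, the calculation supports 8, and either size exceeds 80% power per group. That is right about power, and it makes 16 the likelier intention. It does not settle the matter: the departing sentence stands in the sample-size section, is worded as a commitment and gives its own reasons.

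Several stronger readings are tempting, and the documents do not support them:

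- *The trial will take an unplanned look and inflate its error rate.* Section 9.4 plans no interim analysis, and no passage describes continuing in the light of results. The 7.6% shows what the text leaves open, not what it prescribes.
- *Two totals were approved.* Nothing shows which number the ethics committee approved, and a total of 22 is written nowhere. It follows only from one reading of an undefined word.
- *The 80% power is misattributed.* Section 4.4 attaches 80% to 8 subjects and presents 11 as an increase in power. That is consistent; only the power at 11 is left unstated.
- *Replacement of withdrawals shows that 11 is wrong.* Section 4.4 does not justify 11 by dropout. Section 7.4 helps only to exclude the reading of 11 as a recruitment margin.

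**Conclusion.** Wrong as written: an internal inconsistency in the planned sample size. Section 4.4 implies 22 men (or 11, if *arm* means the whole cohort) against 16 in the Summary and Sections 3 and 4.1. On the likelier reading the gap is 6 men, or 37.5% of 16.

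What is undefined is the end of recruitment and the number of healthy men exposed to metformin and PET-CT. Neither size is underpowered: 85.6% per group at 8 and 96.1% at 11. Those figures rest on the effect and standard deviation in Section 4.4 and on its paired t-test. Section 9.1 names a different test for the before/after comparison, which is a separate matter. The possible rise in two-sided error to about 7.6% is a secondary reason to act and holds only under the worst-case rule in Step 5.

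**What to change.** - Choose one per-group number and one total, and state both identically in the Summary and in Sections 3, 4.1 and 4.4. Replace *arm* with lean group and obese group.
- Give the power for that number under the stated sizing test: about 86% per group at 8, or about 96% at 11, by paired t-test.
- State that recruitment stops at that number irrespective of results.
- If 16 is intended, delete the last sentence of Section 4.4. If 11 per group is intended, change the other three places to 22 in total.

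The cost is a text correction. If the chosen number differs from the one that received the ethics committee's favourable opinion, in either direction, the change should be handled as an amendment under the Amendments section (10.8).

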## **5. TREATMENT OF SUBJECTS**

### **5.1 Investigational product/treatment**

Participants should use metformin twice a day ( 500mg in the morning and 500mg in the evening) during 7 days.

### **5.2 Use of co-intervention (if applicable)**

During the entire study, participants should not take any kind of medication and/or drugs. If, in any case medication is used, they should informing the study-doctor.

### **5.3 Escape medication (if applicable)**

N/A

## 6. NON-INVESTIGATIONAL PRODUCT

Metformin

### 6.1 Name and description of non-investigational product(s)

Metformin

### 6.2 Summary of findings from non-clinical studies

See Summary of Product Characteristics (SPC)

### 6.3 Summary of findings from clinical studies

See SPC chapter 5.1, page 7

### 6.4 Summary of known and potential risks and benefits

See SPC page 2, 6 & 9

### 6.5 Description and justification of route of administration and dosage

Normally, when metformin is given to a patient, the mean starting dose is 500mg 2 or 3 times a day. Therefore, we chose the lowest starting dose of 500 mg twice a day. Furthermore, metformin can only be given orally.

### 6.6 Dosages, dosage modifications and method of administration

Subjects will use the metformin 500mg twice a day, orally.

### 6.7 Preparation and labelling of Investigational Medicinal Product

Preparation and labelling of the investigational medicinal products will be done according to the relevant GMP guidelines (annex 13 of the guideline Good Manufacturing Practice (2003/94/EG, via [http://ec.europa.eu/health/files/eudralex/vol-4/2009\\_06\\_annex13.pdf](http://ec.europa.eu/health/files/eudralex/vol-4/2009_06_annex13.pdf) ))

### 6.8 Drug accountability

The “kenniscentrum geneesmiddelen onderzoek” at the AMC will order and distribute the metformin. The empty metformin packets will be returned to the “kenniscentrum geneesmiddelen onderzoek” after the local researcher has performed drug accountability.

## 7. METHODS

### 7.1 Study parameters/endpoints

#### 7.1.1 Main study parameter/endpoint

Difference in  $^{18}\text{F}$ -FDG uptake as registered by  $^{18}\text{F}$ -FDG PET-CT before and after 7 days of daily metformin use.

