#### i. Predictability of effect

In our retrospective study, 88% of the subjects using metformin had a high F-FDG-uptake in the colon.

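### The protocol specifies no masked reading and no region or SUV rule for its primary PET-CT endpoint, so in this fixed-order, uncontrolled design a reader shift between visits could not be separated from the metformin effect

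*Protocol*

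**What the plan says.** **Design.** The Summary calls this a "Non-randomized interventional study". Section 3 has every participant studied before and after one week of metformin and describes no placebo, untreated arm or randomised order. It states that after the second "visit, subjects will receive the metformin and information on how to use this". The scan at the third visit is therefore always the on-drug scan.

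**Endpoint.** Section 7.1.1 defines the main parameter as the difference in FDG uptake on "PET-CT before and after 7 days of daily metformin use". On measurement, Section 3 says "Glucose uptake in the colon will be evaluated using" PET-CT and no more. Section 7.2 refers back to Section 3 for the detail of procedures. Section 9.1 names a Mann-Whitney U test for the before/after difference and again for lean versus obese. None of these sections names a reader, a region of interest, an SUV measure (maximum or mean) or masking.

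**Target effect.** Section 4.4 says "we aim to find an increase in SUV of 2,8 g/L in the colon" and describes this as "an increase from grade 1 to grade 3 based on a visual scale".

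**Prior expectation.** Section 11.1 i reports that in the team's own retrospective study "88% of the subjects using metformin had a high" colonic uptake. Section 11.1 c uses the same figure to justify a small study.

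**The concern.** Treatment status and scan order are the same variable here: scan one is off drug and scan two is on drug, for every man. The primary inference rests on one within-man difference, and no comparator could reveal or subtract a shift in how the two scans are read.

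An SUV is a number, but it depends on where in the colon the region is placed and on which SUV measure is taken, and the protocol fixes neither. The Introduction notes that a substantial share of people (42% is given as an example) show raised uptake without metformin, so the baseline scan also calls for judgement. A reader who knows which scan is on treatment, and expects it to be hot, could place regions differently on the two scans.

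This is not a detail that can wait for the analysis stage. Once scans have been read with the visit known, those readings cannot be made masked; the scans would have to be read again.

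**Working it through.** **Inputs from Section 4.4:** target difference 2.8 SUV (2.7 to 5.5); SD of differences 2.24; paired t-test; two-sided alpha 0.05; 80% power with 8 subjects.

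**Inputs on numbers enrolled:** Section 3 gives 8 lean plus 8 obese men (16). Section 4.4 ends with 11 per arm (22).

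**Assumption:** an upward reader shift b on the second scan of 0.5 to 1.0 SUV, which is 0.5/2.8 = 18% to 1.0/2.8 = 36% of the target. The documents give no value.

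**Step 1. Reproduce the plan's own figure.** Exact power comes from the noncentral t with n − 1 degrees of freedom and noncentrality (2.8/2.24)·√n.
- n = 7: noncentrality 3.31, power 78.6%.
- n = 8: noncentrality 3.54, power 85.6%.

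Eight is the smallest n with at least 80% power, so the stated size reproduces. Masked reading changes none of these inputs.

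**Step 2. Effect of a shift on the estimate.** If the true change is δ and the second scan is read b too high, the expected mean difference is δ + b. The bias equals b whatever the sample size.

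**Step 3. Effect on the false-positive rate.** Set δ = 0 and use the test from Section 4.4, with noncentrality (b/2.24)·√n.

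| n | b = 0.5 | b = 1.0 |
|---|---|---|
| 8 | noncentrality 0.63, 8.5% | noncentrality 1.26, 19.5% |
| 11 | 0.74, 10.3% | 1.48, 26.8% |
| 16 | 0.89, 13.3% | 1.79, 38.7% |
| 22 | 1.05, 17.0% | 2.09, 51.5% |

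For scale, at n = 8 the observed mean difference must reach 2.365 × 2.24/√8 = 1.87 SUV to be significant.

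**Step 4. The test that Section 9.1 names.** Mann-Whitney treats the two scans as independent samples, so its rejection rate depends on the within-man correlation, which the documents do not give. Simulation with normal data and SD of differences 2.24, at assumed correlations 0 / 0.3 / 0.5 / 0.7:
- n = 8: b = 0.5 gives 7% / 4% / 2% / 0.5%; b = 1.0 gives 18% / 10% / 6% / 2%.
- n = 16: b = 0.5 gives 13% / 7% / 3% / 1%; b = 1.0 gives 38% / 25% / 15% / 5%.

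The paired-t figures are thus approached only near zero correlation. With exact p-values at n = 8 and zero correlation, a repeat simulation gave about 9% and 21%, slightly above the paired-t values. Hence roughly upper bounds, not strict ones. The bias in the estimate (Step 2) does not depend on the test.

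**Step 5. Lean versus obese.** A shift b common to both groups contributes b − b = 0 to the contrast in change. Only a shift that differs by BMI group matters. If it differs by b, with 8 per group and a two-sample t-test on changes (SD 2.24 in each), the noncentrality is b/(2.24·√(2/8)) = b/1.12. That is 0.45 for b = 0.5 (false-positive rate 7.0%) and 0.89 for b = 1.0 (13.2%).

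**The case against.** The strongest reply is that the protocol is silent, and silence is not a statement that reading is unmasked. Reading rules may sit in an analysis plan or imaging document that is not at hand. A reader might infer that scans are read as acquired, with date and treatment status known; nothing in the protocol says so. This stands. What also stands is that the protocol refers the reader to Section 3 for its procedures and sets no safeguard there for its primary measurement.

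A second reply is that the endpoint is numeric. A reader might infer from Section 4.4 that scans are graded by eye. That section only uses the visual scale to explain how large 2.8 SUV is, and no section has anyone assign a grade. This also stands: the route for bias is region choice and SUV measure, not visual grading.

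Third, the size is unknown. It would be too strong to say that reader expectation does add to the effect. The shift is assumed, and the false-positive figures use the Section 4.4 test, not the one in Section 9.1. At n = 8 a small shift alone would seldom give a significant result.

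Fourth, knowledge of BMI group does not in itself bias a within-man difference, and the documents state no expectation by BMI group. Masking to body size is also limited, because it shows on CT.

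These replies limit what can be claimed. None supplies a means of telling a reader shift from a drug effect.

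**Conclusion.** The point holds as a gap in how the primary endpoint is measured, not as evidence of biased reading. The protocol specifies neither masked reading nor a region or SUV rule. With a fixed off-then-on order, no control group and a stated directional expectation, a reader shift by visit would pass in full into the estimated metformin effect and could not be identified afterwards.

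Its size cannot be derived from the documents. The 8.5%–19.5% (8 men) and 13.3%–38.7% (16 men) false-positive rates are illustrations. They assume a constant shift of 0.5 to 1.0 SUV, no true effect, SD of differences 2.24 and a paired t-test; under the Mann-Whitney test in Section 9.1 they are roughly upper bounds. The lean-versus-obese comparison is affected only if the shift differs between groups.

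The change should be made: it is cheap, protects the only primary inference, and has to be in place before scans are read.

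**What to change.** Add to Sections 7.1.1 and 7.2:
- PET-CT scans are stored under a code, with date and visit removed.
- They are read in random order, after a man's second scan or at study end, by one reader masked to visit, and to BMI group as far as the images allow.
- One colon region definition and one SUV measure, written down beforehand, apply to both scans.
- SUV values are locked before the visit order is released.

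**Cost.** Coding and shuffling of 2 × 16 = 32 scans, or 2 × 22 = 44 if 11 men per arm are enrolled, and a short delay before results. No extra scan, subject or reader is needed, and the sample size does not change.

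**Limits.** Masking may be imperfect if uptake on metformin looks characteristic. It deals with reader bias only; order and period effects of the fixed, uncontrolled sequence remain.
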